### 2.12. Ethical Considerations

The study complies with the ethical standards of the Declaration of Helsinki and all procedures were approved in June 2021 by the Institutional Research Ethics Review Board of the Balearic Islands Health Service (CEI-IB Ref No: IB4495/21PI). Participants’ consent will be obtained, and all data collected will be kept confidential and anonymous. As specified in the informed consent, in case of withdrawal, all data collected prior to patient withdrawal will be retained and used by the study investigators. Participants can voluntarily withdraw their informed consent at any time during the study.

### 2.13. Validity and Reliability

This study may generate new evidence about the impact of mHealth interventions in the area of T2DM prevention. The results of the trial are likely to offer a strong internal validity, as we will follow a randomization process based on allocation sequence generation, blinded to the personal investigator and research staff involved in the study. There will be no potential for recruitment bias because randomization will occur after actual participants are enrolled. A pilot study will be conducted during the initial phase of the trial to assess the appropriateness of intervention messages and determine the feasibility of logistic procedures. The study interventions are based on official guidelines and the latest scientific evidence. Data collected with questionnaires might be subjected to potential reporting biases. Nevertheless, this study will mainly use validated questionnaires with robust psychometric properties. Moreover, objective measures (biochemical and anthropometric parameters) will be collected, including the primary outcome HbA1c.

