### 2.6. Randomization and Masking

Family physicians or nurse participants in the study will be randomized by computer-generated random numbers to one of the three arms of the study. Patients from each physician’s or nurse’s will be invited to participate and will receive the intervention according to their physician or nurse arm allocation: Arm 1: healthcare professionals will receive online training and their patients will receive SMS; Arm 2: their patients will receive SMS; Arm 3 (control group): usual care. Outcome assessors will be blinded to treatment allocation.

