### 2.8. Participant Timeline

Table 2 provides an overview of the time schedule of enrolment, interventions, main study visits and assessment measures for participants. Each of the visits is explained in detail below.

Visit −3 (day −60/−45): Invitation to participate. Potential eligible primary healthcare professionals will receive the invitation by email. Once they agree to participate and sign the informed consent form, will be randomized. Potentially eligible participants will receive the invitation by SMS.

Visit −2 (day −45/−7): Participants’ recruitment and baseline interview. The research assistant will contact potential participants via phone. On this call, patients will be given thorough information on the study and, if willing to participate, they will be asked for informed consent. On the same call, a basal interview (behavioural and psychological outcomes) will be performed.

Visit −1 (day −7/−1): Baseline data collection. Participants who signed the informed consent will undergo baseline data collection at the hospital (anthropometric measurements, blood pressure and blood laboratory examinations).

Visit 0 (day 0): Initiation of the intervention. Patients in the Intervention A and Intervention B group will receive their first SMS. Patients in the control group will be informed of their allocation. Health professionals who have been assigned to the intervention B group will take the online education. They will have 4 weeks to complete it.

Visit 1 (month 6): Post intervention data collection. After 6 months of intervention, data collection from patients will be performed following the same procedure as at baseline time basal interview. Interview on behavioural and psychological outcomes will be conducted by phone, and anthropometric measurements, blood pressure and blood laboratory examinations at the Clinical trial Platform at IdISBa. Data collection from health professionals will also be accomplished during this time, through individual interviews (only with Intervention B group professionals) and by delivering an online questionnaire.

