**Participants—patients**					
Invitation by SMS	X				
Informed consent		X			
Inclusion/exclusion criteria		X			
SB assessment ^2^		X			X
Dietary assessment ^3^		X			X
Motivation Questionnaire (ad hoc) ^4^		X			X
PA assessment ^5^		X			X
Randomization ^6^			X		
Blood laboratory examinations ^7^			X		X
Anthropometric measurements ^8^			X		X
Blood pressure measurement ^9^			X		X
Initiation of the intervention ^10^				X	
Trial feasibility: follow-up rate					X

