**Participants—health care workers**					
Invitation by email	X				
Informed consent	X				
Inclusion/exclusion criteria	X				
Randomization	X				
Online education (intervention B group)				X	
Individual interviews (intervention B group)					X
Interview: Knowledge and attitudes about prediabetes, and communication skills					X
Trial feasibility: follow-up rate					X

1. Time point: d = day; m = month; 2. SB assessment: NHS questionnaire; 3. Dietary assessment: MedDiet adherence questionnaire; 4. Motivation Questionnaire (ad hoc); 5. PA assessment: REGICOR PA questionnaire; 6. Randomization: Patients and healthcare workers will be randomised at the same time, with only the healthcare worker being randomised, and their 10 patients being assigned to the same intervention group as the healthcare workers; 7. Blood laboratory examinations: glucose, HbA1C, total cholesterol, HDL-c, LDL-c, TG, Hb, MCV, serum creatinine, AST, ALT, and GGT. TyG index and FLI will be calculated; 8. Anthropometric measurements: body weight, WC and HC, BMI, body composition, height; 9. Blood pressure measurement: the arm with the highest blood pressure. Subsequent blood pressure measurements will be taken in this arm throughout the study; 10. Initiation of intervention: initiation of SMS sending.

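### Section 2.13 rules out recruitment bias because randomisation follows enrolment, but Section 2.8 and part of Table 2 allocate professionals before any patient consents

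*Protocol article*

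**What the plan says.** The protocol article describes the order of randomisation and enrolment in several places.

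- Section 2.13 gives a validity assurance with a single reason: "There will be no potential for recruitment bias because randomization will occur after actual participants are enrolled".
- Section 2.8, Visit −3, says of the professionals: "Once they agree to participate and sign the informed consent form, will be randomized". The next sentence of the same visit concerns patients: "Potentially eligible participants will receive the invitation by SMS".
- Section 2.8, Visit −2, places patient consent on a later phone call: "On this call, patients will be given thorough information on the study and, if willing to participate, they will be asked for informed consent". The baseline interview takes place on that call. Anthropometry, blood pressure and bloods follow at Visit −1.
- Section 2.6 first randomises physicians and nurses, then says that their patients "will be invited to participate and will receive the intervention according to their physician or nurse arm allocation".
- Table 2 has a row labelled "Randomization" in each block. In the professionals' block it is marked at Visit −3; in the patients' block it is marked at Visit −1.
- Footnote 6 to that table says: "Patients and healthcare workers will be randomised at the same time, with only the healthcare worker being randomised".

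**The concern.** In a cluster trial, randomising the professionals balances the professionals and the pool of patients they look after. It does not by itself balance the patients who later agree to take part. If patients are recruited into clusters that already have an arm, the explanation given on the phone, or the kind of patient who agrees, can differ between arms. Adjustment for the baseline value of the outcome, as planned in Section 2.11, removes only the part of such a difference that the baseline value captures.

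Section 2.13 excludes this risk outright, and its stated reason is the order of events. If the order is the reverse, the assurance has no basis, and it could be carried into the trial report as a design strength. The selection check in Section 2.11 does not replace it: that check compares people recruited with all who were eligible, which addresses representativeness rather than comparability of arms.

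**Working it through.** No statistical figure underlies the claim. The check sets the stated times side by side.

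1. Professional randomisation: Visit −3, day −60 to −45 (Section 2.8; professionals' block of Table 2).
2. Patient SMS invitation: also Visit −3 (Section 2.8; patients' block of Table 2).
3. Patient consent and baseline interview: Visit −2, day −45 to −7 (Section 2.8; Table 2 for consent).
4. Baseline clinical measurements: Visit −1, day −7 to −1 (Section 2.8; Table 2).
5. Patient randomisation row: Visit −1 (patients' block of Table 2).
6. Start of SMS and of online education, and control patients told their arm: Visit 0, day 0 (Section 2.8).

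**Gap between allocation and consent under items 1 and 3.** The shortest is 45 − 45 = 0 days and the longest is 60 − 7 = 53 days. Every cluster is therefore allocated before, or at the latest when, the patient consent window opens.

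**Gap between allocation and baseline clinical measurement under items 1 and 4.** The shortest is 45 − 7 = 38 days and the longest is 60 − 1 = 59 days. All baseline clinical data come after allocation.

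**Items 1 and 5 against footnote 6.** The footnote says that professionals and patients are randomised together and that only the professional is actually randomised. There is then one randomisation event per cluster, and it cannot fall at both Visit −3 and Visit −1. The footnote does not say which. If the event is at Visit −1, it follows patient consent and Section 2.13 is right about the order. If it is at Visit −3, patients are assigned before they have consented and Section 2.13 is wrong.

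**Section 2.6.** It names no visit, but its sequence (professionals randomised, patients then invited and following that arm) fits Visit −3. So does Section 2.4.2, which draws the patient list from professionals already recruited, because Section 2.8 randomises professionals once they have consented.

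**Can the participants in Section 2.13 be read as the professionals?** They are indeed enrolled before they are randomised. This does not rescue the assurance, because patients would still be recruited afterwards into allocated clusters, and that is where recruitment bias in a cluster trial arises.

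**The case against.** The strongest reply is that an allocation that exists is not an allocation that anyone recruiting knows. Section 2.13 says that the randomisation process is blinded to the investigator and research staff, and Section 2.8 tells control patients their arm only at Visit 0, after consent and baseline. Section 2.4.2 adds safeguards. Patients are found in electronic records by laboratory criteria and approached starting from the most recent blood tests, and a research assistant, not the allocated professional, makes the call. No role for the professional in choosing or consenting patients is described.

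Much of this stands, and it rules out two stronger readings.

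- A reader might infer that patients are recruited under known allocation. The documents do not say so. Table 1 describes the trial as open label and Section 2.6 names only outcome assessors as blinded, but neither says who knows the arm at the time of consent.
- A reader might infer that randomisation precedes every invitation. The order of the text suggests it, but both events share Visit −3 and nothing fixes which comes first. Only precedence over consent is supported.

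The Visit −1 row is also part of the schedule, and Figures 3 and 4, which may show the order, are not available here. It would therefore be too strong to call the Section 2.13 sentence simply false. Finally, counts and baseline tables by arm are details that an article may leave to the full protocol or analysis plan, so their absence is not part of this point.

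What the reply does not save is the sentence itself. It excludes recruitment bias because of timing, and the visit text contradicts that timing. Approaching patients by date of blood test limits the choice of whom to phone, not who agrees. The article does not say how the assistant is kept unaware of the arm, or when professionals learn theirs.

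**Conclusion.** The point holds as a contradiction about a stated design property. Sections 2.6 and 2.8 and the professionals' block of Table 2 place allocation before patient consent. Section 2.13 and the patients' row of Table 2 place it after. Footnote 6 is incompatible with the two different marks in its own table.

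Under the Visit −3 schedule, the reason given for excluding recruitment bias fails for all 420 planned patients, with allocation up to 53 days before consent. Timing then does not secure concealment during consent and baseline measurement. Under the Visit −1 reading the reason stands. Which schedule is meant cannot be decided from the text shown.

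The size of any resulting bias is unknown. It would depend on whether recruiters or patients learn the arm before consent, which the documents do not state, and on how far consent then differs between arms, for which they give no figure. The conclusion rests only on the stated visit windows.

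**What to change.** Reconcile the sections so that each professional is randomised, or at least the allocation is released, only after his or her patients have consented and completed the Visit −1 baseline measurements. This means removing randomisation from Visit −3 in Section 2.8, moving the mark in the professionals' block of Table 2 to match the patients' row, stating the single time point in footnote 6, and making the sequence in Section 2.6 agree. The reason given in Section 2.13 would then be true.

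The cost is small. SMS and online education both start at Visit 0, and nothing described earlier needs the allocation. No visits or patients are added; professionals learn their arm some weeks later. Day 0 should then be set for a professional's patients as a group, since release waits for the last of them to finish Visit −1.

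If Visit −3 randomisation is kept, and for any clusters already randomised (Table 1 lists the trial as recruiting):

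- withdraw the sentence that excludes recruitment bias;
- keep the recruiting research assistants and the patients unaware of the arm until baseline is complete, and say how;
- report numbers approached and consented, and baseline characteristics, by arm.

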## 3. Discussion

In Spain, more than 4 million people suffer from T2DM. It is well established that T2DM can be effectively prevented through lifestyle changes, but patients at risk of T2DM do not always receive adequate advice on recommended changes in diet and physical activity. Moreover, strategies to provide ongoing and effective support and motivation are not well developed and facilitating sustained behaviour change remains a major challenge.

The interventions proposed in this study have the potential to contribute to addressing this important problem. Two systematic reviews by members of our team show that automated brief text messages sent to mobile devices effectively promote lifestyle changes [14] and medication adherence [49]. We propose these types of interventions not only because they are likely to be effective but also because of their high translational value. They can be delivered at low cost (clear potential for cost-effectiveness) and easily implemented widely (high scalability), therefore constituting a sustainable strategy for Health Services to improve health at the population level. This technology-based solution is highly transferable as it could also be adapted for its use in other settings and groups of patients. In addition, the intervention would offer, in times of pandemic, a feasible alternative to face-to-face consultations for people with prediabetes, with a personalized lifestyle change, using preventive strategies.

These interventions would enable personalized remote health care for a broad population including socially vulnerable populations. This is of particular relevance in view of the affection of T2DM in this population group and the difficulties of access, and therefore representation, of this population group in clinical trials.

Telemedicine has increased during the COVID-19 pandemic, becoming a very important resource for improving healthcare management, especially in primary care, supervised by multidisciplinary teams, consisting mainly of nurses and GPs [50]. Implementing mHealth interventions by nurses for the prevention of T2DM could reduce healthcare costs and reach larger populations.

### Limitations

The study has several limitations. First, due to the nature of the intervention, participants will be aware of their treatment allocation. Second, involving primary healthcare professionals through online intervention may be unfeasible if the COVID-19 pandemic continues hitting our region with high intensity. Finally, the proposed phase II trial is not powered to determine the effectiveness of the proposed interventions in preventing T2DM. However, it will provide valuable information to determine the feasibility of the trial procedures and to explore the potential impact of the intervention in terms of reduction of HbA1c. We plan to conduct a fully powered phase III trial in case positive results are obtained from this study.

## 4. Conclusions

The realization of the present project is key for several reasons: (1) The incidence of type 2 diabetes and pre-diabetes is increasing, and consequently, the associated comorbidities, loss of quality of life, and loss of autonomy; (2) The direct health costs and indirect costs for type 2 diabetes treatment, as labour cost due to lack of productivity, are an important economic burden for many countries. Interventions to prevent the development of type 2 diabetes are needed; (3) The development of a low-cost, easy-to-implement intervention is crucial to address a problem that affects a large vast of population. For all the aforementioned, findings from this study will contribute to solving a real and urgent problem of society, contributing to addressing type 2 diabetes mellitus prevention through a low-cost and easily implementable intervention.

## Figures and Tables

**Figure 1 ijerph-19-14706-f001:**
[figure not shown]
PreDiabeText project overview.

**Figure 2 ijerph-19-14706-f002:**
[figure not shown]
Description of the PreDiabeText Technological System for the messaging intervention. Three databases are combined using specific algorithms in order to produce a text file containing the information to be uploaded to the SMS delivery platform, which will send personalized SMSs to the study participants.

**Figure 3 ijerph-19-14706-f003:**
[figure not shown]
Consort flowchart of the PreDiabeText phase II clinical trial.

**Figure 4 ijerph-19-14706-f004:**
[figure not shown]
Phase II PreDiabeText study timeline.

**Table 1 ijerph-19-14706-t001:** Brief structured summary of the trial.

Data Category	Information
Trial identification number	ClinicalTrials.gov NCT05110625
Date of registration	8 November 2021
Sponsor	Balearic Islands Research Institute (IdISBa), Spain
Contact for public and scientific queries	[name] [name]. Primary Care Research Unit of Mallorca (IB-Salut), Balearic Health Service, Palma de Mallorca, Spain, Palma de Mallorca, [contact]
Scientific title	Effects of a low intensity, multifaceted, mHealth intervention to prevent type 2 diabetes mellitus in adults with prediabetes in the primary care setting (the PREDIABETEXT trial)
Country of recruitment	Spain
Health condition studies	Prediabetes
Interventions	Intervention A: Participants will receive text messages (three per week) in their mobile phones during six months Intervention B: Participants will receive messaging intervention plus online education to their primary healthcare workers
	Control: Participants will receive usual care only, and their healthcare workers will not receive online education
Inclusion/exclusion criteria	Eligible age: 15–75 years; eligible sex: males and females.
	Inclusion criteria: Registered in the Public Health Service of the Balearic Islands. HbA1c from 6% to 6.4% or fasting plasma glucose 110–125 mg/dL, or both. With access to a mobile device able to receive text messages.
	Exclusion criteria: documented history of T2D and/or use of oral antidiabetic medication. Younger than 18 years old or older than 75 years old. People not able to read messages in Spanish. Patients with severe mental conditions.
Study type	Interventional
	Allocation: randomized; Intervention model: parallel assignment; masking: none (open label)
	Primary purpose: Change from Baseline HbA1C at 6 months
Date of first enrolment	1 September 2021
Target sample size	420 (140 participants in each group)
Recruitment status	Actively recruiting
Primary outcomes	Reduction of HbA1C
Secondary outcomes	Fasting blood glucose, body weight, waist circumference, blood pressure, lipids, cardiovascular disease risk, proportion of patients developing T2DM, adherence to Mediterranean diet, physical activity, sedentary behaviour, smoking habit, alcohol consumption

**Table 2 ijerph-19-14706-t002:** Participants main visits and assessment schedules.

Main Visits and Assessment Schedules					
Visit	V −3	V −2	V −1	V 0	V 1
Time point ^1^	−60 d	−45 d	−7 d	0 d	6 m
**Participants—patients**					
Invitation by SMS	X				
Informed consent		X			
Inclusion/exclusion criteria		X			
SB assessment ^2^		X			X
Dietary assessment ^3^		X			X
Motivation Questionnaire (ad hoc) ^4^		X			X
PA assessment ^5^		X			X
Randomization ^6^			X		
Blood laboratory examinations ^7^			X		X
Anthropometric measurements ^8^			X		X
Blood pressure measurement ^9^			X		X
Initiation of the intervention ^10^				X	
Trial feasibility: follow-up rate					X
**Participants—health care workers**					
Invitation by email	X				
Informed consent	X				
Inclusion/exclusion criteria	X				
Randomization	X				
Online education (intervention B group)				X	
Individual interviews (intervention B group)					X
Interview: Knowledge and attitudes about prediabetes, and communication skills					X
Trial feasibility: follow-up rate					X

1. Time point: d = day; m = month; 2. SB assessment: NHS questionnaire; 3. Dietary assessment: MedDiet adherence questionnaire; 4. Motivation Questionnaire (ad hoc); 5. PA assessment: REGICOR PA questionnaire; 6. Randomization: Patients and healthcare workers will be randomised at the same time, with only the healthcare worker being randomised, and their 10 patients being assigned to the same intervention group as the healthcare workers; 7. Blood laboratory examinations: glucose, HbA1C, total cholesterol, HDL-c, LDL-c, TG, Hb, MCV, serum creatinine, AST, ALT, and GGT. TyG index and FLI will be calculated; 8. Anthropometric measurements: body weight, WC and HC, BMI, body composition, height; 9. Blood pressure measurement: the arm with the highest blood pressure. Subsequent blood pressure measurements will be taken in this arm throughout the study; 10. Initiation of intervention: initiation of SMS sending.

## Data Availability

Not applicable.

